### Inclusion criteria

Patients meeting the following criteria will be considered for eligibility:Aged over 65Informed consent and voluntary participation in a clinical trialDiagnosed with acute hip fracture induced by low-energy injury including intertrochanteric fracture and FNF within 14 days before admissionIn at least one of the following conditions:aType 2 diabetes mellitus (T2DM)bChronic lung disease such as chronic obstructive pulmonary diseasecPre-injury activities of daily living (ADL) score < 60dModified British Medical Research Council (mMRC) score ≥ 2eFirst result of leukocyte count > 10 × 10^9^/L or C-reaction protein (CRP) > 15 mg/L at emergency visits (EV)fFirst result of PaO_2_ < 80 mmHg or SaO_2_ < 96% at EVgFirst result of hemoglobin < 100 g/L at EVhFirst result of serum albumin < 35 g/L at EViPrevious history of smoking and sleep apnea syndrome

5.Able to tolerant the prone position for at least 30 min one time6.Intertrochanteric fracture patients receiving closed reduction and internal fixation (proximal femoral locking gamma nail); FNF patients receiving posterior approach uncemented total hip arthroplasty (THA) or hemiarthroplasty (HHA) as procedure methods

### Exclusion criteria

Patients meeting the following criteria will be considered for exclusion.With life-threatening organ dysfunction, or unable to disengage from guardianship or non-invasive/invasive oxygen supplementWith pulmonary comorbidities which have the same name as sub-diseases of PPCs before surgeryWith osteosarcoma, multiple myeloma, and various other pathological fracturesWith multiple fractures or severe vascular, nerve, or soft tissue injury injuriesWith a bilateral hip fractureReceiving hip revision surgeryWith a history of major cardiac or pulmonary surgeryIn an immune-disorder condition caused by various causes (malignant tumors, severe autoimmune diseases, long-term hormone use, etc.)

### Baseline data

Baseline data will include gender, age, body mass index, type of fracture, time from injury to surgery, pre-injury ADL score, mMRC score, American Society of Anesthesiologists classification, comorbidities including pulmonary disease according to the first result of thoracic computerized tomography (CT) at admission (atelectasis, pleural effusion, chronic obstructive pulmonary disease), hypertension, T2DM, coronary atherosclerotic heart disease, cognitive dysfunction, prior stroke, cerebral infarction, history of smoking and drinking, first laboratory results of arterial blood gas analysis [PaO_2_, PaCO_2_, SaO_2_, pH, lactic acid], routine blood test (erythrocyte count, leukocyte count, CRP, hemoglobin), biochemistry test (serum albumin, blood glucose, blood creatinine, blood urea nitrogen), electrolyte test (serum potassium, serum sodium), D-dimer, brain natriuretic peptide (BNP) at EV, time from injury to surgery, proportion of receiving surgery within 48 h after admission, surgical procedures (closed reduction and internal fixation, THA or HHA), methods of anesthesia (general or epidural anesthesia), postoperative respiratory failure risk index [28] (Additional file 3), POP risk index [29] (Additional file 4), duration of surgery, perioperative blood transfusion volume.

### Randomization and allocation

Randomization will take place once participants have signed informed consent for the surgical procedure. SAS software 9.4 will be used to generate the random table as an allocation sequence by an investigator (LS) and random numbers will be assigned by the envelope method. Based on random numbers, another investigator (TX) will assign patients to the APP group or control group in a 1:1 ratio. Details of any planned restriction will be provided in a separate document that is unavailable to those who enroll participants or assign interventions.

### Blinding

Keeping trial participants and care providers blinded is unrealistic. But neither the outcome assessors nor the data analysts are aware of the grouping. Grouping information will be represented to data analysts in the form of group A/B rather than the APP group and control group. During the data analysis phase, all personal information that can be used to identify the participants will be hidden.

### Intervention

After signing informed consent, participants will be enrolled and randomly assigned to either the APP group or the control group. Surgical treatment will be performed on an emergency basis upon completion of the necessary pre-operative preparations. The surgical procedures, including closed reduction and internal fixation, THA, and HHA, will be decided by the chief physician (HC and YR) in trauma orthopedics. All operations will be scheduled in a fixed operating theatre and completed by the same team. Patients in the APP group will receive the prone position for at least half an hour at a time, and at least once per day for the first three consecutive PODs. The first APP treatment each day will be guided and supervised. The frequency and duration of other spontaneous prone positions of patients in the APP group will not be constrained. Except for this, during this period, all patients will receive the same postoperative management including postoperative oxygen inhalation (2L/min) for 6 h, standardized nutritional support, anti-inflammatory, detumescent, analgesic, hypodermic anti-coagulant prophylaxis, and regular atomization therapy. Both FNF and intertrochanteric fracture patients will roll onto their broken side into a prone position. Prone position pads will be used to suspend the upper abdomen and chest to reduce intra-abdominal and intra-thoracic pressure, allowing the alveoli to expand sufficiently. If severe adverse events such as unbearable pain, suspected prosthesis dislocation or internal fixation failure, chest tightness, and difficulty breathing occur, or the patients report that he/she cannot tolerate the prone position, the intervention should be stopped immediately. The investigators’ department will treat and compensate the patient for any additional injuries resulting from APP treatment. Intervention time as an adherence quantitative indicator and the reasons for intervention termination will be recorded in the database. Hematological parameters and chest radiography will be re-examined on the morning of POD 4. Patients will be followed up for at least 90 PODs through outpatient visits or telephone calls. In addition to orthopedic-related tests, they will undergo chest CT in an outpatient setting to determine if PPCs are present. The conduct of the trial will be audited weekly, independently of the investigators.

*Standard of discharge*: (1) The x-ray shows that the position of the internal fixation/prosthesis is in place. (2) The incision is essentially healed, and no signs of infection are found. (3) No serious complications have occurred requiring continued hospitalization. (4) The serological test results and the general condition of the patient are acceptable.

### Primary outcome

The primary outcome of the study will be the incidence of PPCs during the first 30 PODs. PPCs include all related diseases (atelectasis, POP, ARDS, pulmonary embolism, pleural effusion, pneumothorax, cardiogenic pulmonary edema, and bronchospasm) diagnosed anywhere.

### Secondary outcome

The secondary outcomes will be PaO_2_ on POD 4, the difference in PaO_2_ between POD 4 and EV, CPIS on POD 4, LOS, other types of postoperative complications, readmission, and mortality in 90-POD follow-up.

Given that FiO_2_ is equal to 20.9% of the breathing room air, we will use PaO_2_ instead of P/F to reflect the patient’s oxygenation capacity. On the morning of POD 4, the patient will undergo arterial blood gas analysis while inhaling room air. We anticipate that postoperative oxygenation (expressed as PaO_2_), will be higher in the APP group than in the control group. To minimize the impact of the baseline oxygenation capacity of different participants on the results, we will use the difference in PaO_2_ between POD 4 and EV to balance out this individual difference. Additional tests required for the diagnosis of complications, such as chest CT, pulmonary and coronary CT angiography, brain CT, arterial blood gas analysis, myocardial X-ray, troponin, and BNP, will be performed as soon as suspicious symptoms such as dyspnea, chest distress, fever, cough, sputum, and motor, sensory or cognitive dysfunction appear. All post-operative complications will be diagnosed following consultation with the appropriate specialist. Readmission and mortality rates within 30 or 90 PODs will be calculated separately. All serious adverse events, as well as all non-serious adverse events that are unexpected and determined to be related to the APP treatment, will be recorded in the study database and reported on request to the IEC for Clinical Research of Zhongda Hospital, Affiliated to Southeast University.

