### Data collection and analysis plan

All data will be collected and stored in case report form by two well-trained assessors (WG, MC) independently. Any discrepancies will be checked by the same two assessors to ensure accuracy and authenticity. All information will be aggregated in the final trial dataset, which will be accessible only to LS and will only be shared with research team members upon request for the completion of the designated learning task. All information related to patient identification will be hidden before being uploaded to a public database. Descriptive analyzes of the patient population will include reporting means (with SDs) for normally distributed variables, medians (with Q1, Q3) for skew-distributed variables, and frequencies (with percentages) for categorical variables. Student t-tests will be conducted to analyze normally distributed variables. The Mann-Whitney *U* test will be used for skew-distributed data and ordered categorical variables. Chi-squared tests will be used to analyze binary or unordered categorical variables. The balance of baseline data and differences in postoperative outcomes will be assessed in terms of the above variables. To control other covariates, including stratification factors (gender and fracture type) and baseline variables that have potential relation with the outcome, as well as any such variable that appears imbalanced between the APP group and control group, multiple logistic regression model will be conducted to analyze the related factors of PPCs at each point of time (POD 30 and 90). Similarly, we will perform a multivariate linear regression analysis to determine which variables are independently related to the difference in PaO_2_ between POD 4 and EV. All analyses will be performed using the SPSS 23.0 software. Any outcome data collected for participants who discontinued or deviated from the intervention protocol will be listed. Primary and secondary outcome analysis will not allow missing data. Other missing values will be assumed to show no significant difference from other data we have collected; If missing values suggest that the missingness is not random, we will assess the potential impact of missing data on our results via a developmental model.

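### The change in PaO2 from emergency visit to POD 4 does not remove baseline differences; the planned regression should be fixed to adjust for baseline PaO2 and serve as the main oxygenation comparison

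*Protocol article*

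**What the plan says.** The Secondary outcome section lists two oxygenation measures side by side: "The secondary outcomes will be PaO_2_ on POD 4, the difference in PaO_2_ between POD 4 and EV". It gives the reason for the second: "we will use the difference in PaO_2_ between POD 4 and EV to balance out this individual difference". It does not say which of the two is the oxygenation result.

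The Data collection and analysis plan section assigns tests by the type of variable. For continuous outcomes, "Student t-tests will be conducted to analyze normally distributed variables", and the Mann-Whitney "test will be used for skew-distributed data and ordered categorical variables". These tests cover the arm comparison: "The balance of baseline data and differences in postoperative outcomes will be assessed in terms of the above variables". None of them uses a covariate.

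The same section then describes multivariable models. The logistic model for PPCs controls for gender, fracture type and "baseline variables that have potential relation with the outcome, as well as any such variable that appears imbalanced" between the arms. By analogy there is to be a "multivariate linear regression analysis to determine which variables are independently related to the difference in PaO_2_ between POD 4 and EV". Neither the treatment arm nor EV PaO2 is named as a term in it.

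EV PaO2 is part of the Baseline data.

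**The concern.** Taking the difference is meant to deal with patients starting from different oxygenation levels. A difference does that completely only if each mmHg at baseline carries through, on average, to exactly one mmHg at POD 4. With any weaker relation the change is negatively related to the starting value: patients who start low tend to rise and those who start high tend to fall, whatever the treatment. A chance difference between the arms in EV PaO2 then passes into the comparison of changes, which is what the subtraction was meant to prevent.

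Three things are at stake: precision, robustness to chance imbalance, and clarity of the result. The two unadjusted comparisons (raw POD 4 and change) can point different ways, with no rule for which one counts. Improved oxygenation appears in the Objective and the Hypothesis alongside PPCs, although it ranks as a secondary research question.

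**Working it through.** **Inputs.** The article gives no SD for PaO2, no correlation r between EV and POD 4 PaO2, and no target difference. Its sample size of 200 is set on 30-day PPCs, so there is no planned figure for PaO2 to reproduce. The calculations below assume r = 0.3, 0.5 and 0.7. They first take equal SDs at EV and POD 4, then vary the ratio λ = SD(EV)/SD(POD 4) from 0.8 to 1.25.

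**1. Does subtraction remove baseline?** With equal SDs, corr(change, baseline) = −√((1−r)/2).
- r = 0.3: −√0.35 = −0.59
- r = 0.5: −√0.25 = −0.50
- r = 0.7: −√0.15 = −0.39

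It would be zero only at r = 1.

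**2. Effect of a chance imbalance.** With equal SDs the regression slope of POD 4 on EV is r. If one arm starts 1 mmHg higher by chance, the expected shift is +r mmHg in the raw POD 4 comparison and r − 1 mmHg in the change comparison.

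| r | Shift in raw POD 4 (mmHg) | Shift in change (mmHg) |
|---|---|---|
| 0.3 | +0.3 | −0.7 |
| 0.5 | +0.5 | −0.5 |
| 0.7 | +0.7 | −0.3 |

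The two unadjusted comparisons move in opposite directions. Adjusting for EV PaO2 removes the shift.

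**3. Precision.** The variance of the arm difference, relative to POD 4 alone (= 1), is 2(1−r) for the change and 1−r² for the baseline-adjusted analysis (ANCOVA). The ratio of change to ANCOVA is 2(1−r)/(1−r²) = 2/(1+r).

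| r | Change | ANCOVA | Change / ANCOVA |
|---|---|---|---|
| 0.3 | 1.40 | 0.91 | 1.54 |
| 0.5 | 1.00 | 0.75 | 1.33 |
| 0.7 | 0.60 | 0.51 | 1.18 |

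Below r = 0.5 the change is noisier than POD 4 PaO2 alone, so subtracting is worse than ignoring baseline.

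**4. Unequal SDs.** The change variance becomes 1 + λ² − 2rλ. It exceeds the ANCOVA variance by (λ − r)², which is never negative. Over λ = 0.8 to 1.25 and r = 0.3 to 0.7 the ratio runs from 0.52/0.51 = 1.02 (λ = 0.8, r = 0.7) to 1.8125/0.91 = 1.99 (λ = 1.25, r = 0.3).

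**5. Simulation check.** In 4,000 simulated trials per value of r, with 80 per arm and SD 10, the standard errors for POD 4 alone, change and ANCOVA were:
- r = 0.3: 1.59, 1.92, 1.54
- r = 0.5: 1.57, 1.59, 1.37
- r = 0.7: 1.62, 1.21, 1.14

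ANCOVA was the most precise each time. The simulated correlations of change with baseline matched step 1.

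**6. What the planned regression could deliver.** Regressing the change on arm and EV PaO2 gives the same arm effect as regressing POD 4 PaO2 on arm and EV PaO2. In the simulation the largest discrepancy was 2 × 10⁻¹⁴, which is rounding error. The model already foreseen would therefore be the ANCOVA if both terms were in it.

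**The case against.** The strongest reply is that the plan already contains the answer. The linear regression follows a rule that admits baseline variables related to the outcome. EV PaO2 is collected, and by the argument above it is related to the change. With arm and EV PaO2 included, the model gives the adjusted effect exactly, and a full covariate list is something an article may leave to a fuller document. This carries weight: a reader might infer that oxygenation is compared only without adjustment, and the article does not support that. But the regression's stated purpose is to find which variables are related to the change. It names neither arm nor EV PaO2, and it lets covariates in partly because they look imbalanced. The article does state positively that subtraction deals with baseline and that outcome differences are assessed with the unadjusted tests, so this is not merely omitted detail.

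Four other stronger readings are tempting and do not stand:
- **Bias.** Under randomisation, regression to the mean acts on both arms alike. The change comparison is unbiased and keeps its type I error. The loss is in efficiency and in sensitivity to chance imbalance.
- **Selection on low PaO2.** A low first PaO2 or SaO2 is one of nine alternative risk conditions in the Inclusion criteria, and any one suffices. The article does not say how many patients enter that way, so it cannot be said that the trial mainly enrols them.
- **A number of patients lost.** One could turn the ratio at r = 0.3 into an equivalent number of wasted patients. That would rest on one unfavourable value of r, on equal SDs, and on applying the 20% loss rate, tied in the Sample size section to the 30-day outcome, to a blood gas on POD 4. Only the range is defensible.
- **A free change.** The trial is recruiting, so a change to the analysis has to be documented and communicated, and the provision for skewed data should not be lost.

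It is also fair that PPCs are the sole primary outcome and that no power is claimed for PaO2.

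**Conclusion.** The concern holds in this form: the stated reason for using the change is incorrect, and the tests assigned to the oxygenation outcomes are less precise than baseline adjustment and exposed to chance imbalance in EV PaO2. With equal SDs the change comparison has 1.18 to 1.54 times the variance of the adjusted one for r between 0.7 and 0.3. With SD ratios of 0.8 to 1.25 the range is 1.02 to 1.99. The direction does not depend on these assumptions, since the adjusted variance is never the larger apart from the degree of freedom spent. The size does, and the article supplies neither r nor the SDs. The planned regression narrows the gap but does not close it, because it is not committed to as the treatment comparison. As this concerns efficiency on a secondary outcome, the change is advisable; the trial's validity does not hinge on it.

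**What to change.** In the linear regression already planned, prespecify arm, EV PaO2 (continuous), gender and fracture type as fixed terms, whatever the observed balance. The response may be POD 4 room-air PaO2 or the change, since the arm effect is identical. State that the adjusted mean difference with its 95% CI is the main oxygenation comparison. Keep the unadjusted comparisons of POD 4 PaO2 and of the change, including the Mann-Whitney option, as supportive. Drop the statement that the difference cancels baseline variation.

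The cost is one degree of freedom for EV PaO2 and a short protocol clarification, communicated as the article foresees for important modifications. No new data are needed: the change itself already requires EV PaO2.

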**Fig. 2 Fig2:**
[figure not shown]
Schedule of enrolment, interventions, and assessments

Patients will undergo a review of hematological parameters including routine blood, biochemistry, electrolyte, and blood gas analysis on POD 4. Clinical pulmonary infection score (CPIS) [27] (Additional file 2) will be calculated on POD 4. The incidence of various postoperative complications, mortality rate, and LOS during hospitalization will be also recorded. At the same time, the incidence of postoperative complications especially PPCs, readmission, and mortality rates will be calculated within 30 and 90 PODs, respectively. This protocol has been approved by the Independent Ethics Committee (IEC) for Clinical Research of Zhongda Hospital, Affiliated to Southeast University (2021ZDSYLL203-P01), and is registered on the Chinese Clinical Trial Registry (ChiCTR2100049311). Only the head of this series of research (YR) has the right to make the final decision to terminate the trial if any serious adverse event judged to be related to the study treatment occurs.

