### Clinical application of prone position treatment

Previous researches have shown that prone position ventilation may reduce the incidence of ventilator-associated pneumonia, but does not reduce mortality in patients with acute respiratory failure and may increase the risk of other complications such as pressure ulcers [44, 45].

However, there still existed a growing body of clinical evidence supporting that the prone position is of positive significance in delaying the progress of pulmonary diseases and improving prognosis. Compared with the left lateral position, patients who underwent thoracoscopic esophagectomy in the prone position had a markedly higher oxygenation index after the surgery, though no significance was found in the PPCs between the two surgical positions [46]. Prone position has been proven to effectively reduce the risk of mortality and length of intensive care unit stay in ventilator-associated pneumonia patients [47]. Moreover, as one of the protective lung ventilation strategies, the prone position could reduce mortality in severe ARDS and acute respiratory failure patients significantly [48–51]. When applicated to conscious patients, the prone position manifested a similar outcome. Early APP combined with noninvasive ventilation or high-flow nasal canula could reduce or delay the need for intubation and the possibility to develop critical patients in moderate to severe ARDS patients with COVID-19 [52, 53]. For acute hypoxia patients, APP was recommended to be carried out early to prevent the worsening of hypoxemia and respiratory failure [41].

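### Non-serious adverse events are recorded only if unexpected and attributed to APP, so minor foreseeable harms not diagnosed as complications cannot be compared between arms

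*Protocol article*

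**What the plan says.** The rule stands in the Secondary outcome section of the protocol article. Its subject is every serious adverse event, plus "non-serious adverse events that are unexpected and determined to be related to the APP treatment", and these events "will be recorded in the study database and reported on request to the IEC for Clinical Research". Entry in the database and reporting to the ethics committee thus share one definition.

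Three other statements bear on how harms are captured:

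- **Complications as an outcome.** The secondary outcomes include "other types of postoperative complications, readmission, and mortality in 90-POD follow-up". The text after Fig. 2 adds: "The incidence of various postoperative complications, mortality rate, and LOS during hospitalization will be also recorded". Neither is limited by arm, cause or expectedness. Secondary outcome also says that every complication is diagnosed after specialist consultation.
- **Stopping the intervention.** The Intervention section stops APP if "severe adverse events such as unbearable pain, suspected prosthesis dislocation or internal fixation failure, chest tightness, and difficulty breathing occur", or if the patient cannot tolerate the position. The reason is entered in the database.
- **Known risk.** The Discussion, under Clinical application of prone position treatment, notes from earlier research that prone ventilation "may increase the risk of other complications such as pressure ulcers".

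**The concern.** A harm comparison needs the same events to be counted in the same way in both arms. This rule makes eligibility for counting depend on the treatment received and on whether the event was foreseen. Pain, skin marks and chest discomfort occur after hip surgery without proning, so a count in the APP arm means little without the control rate.

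The stakes are the balance of benefit and harm, not the primary outcome. The trial is meant to support using APP in elderly hip-fracture patients on a general ward. The safety record cited in the Discussion is that none of 42 preliminary APP patients had prosthesis dislocation or fixation failure; it is silent on pain and skin. Candidates for enrolment are nevertheless told that earlier experience showed APP to be safe (Setting and participants). The randomised comparison is the natural place to measure the minor harms.

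**Working it through.** No figure in the plan is at issue, so there is nothing to recompute. The check is to follow each kind of event through every recording route in the article.

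**Inputs**

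1. Route A, adverse events (Secondary outcome): recorded if serious, or if non-serious AND unexpected AND attributed to APP.
2. Route B, complications (Secondary outcome; text after Fig. 2): recorded in either arm if diagnosed as a postoperative complication.
3. Route C, stopping reasons (Intervention): recorded when APP is ended, so open to the APP arm only.

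**Result by type of event**

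| Event | APP arm | Control arm |
|---|---|---|
| Serious, any cause | Recorded (A) | Recorded (A) |
| Non-serious, diagnosed as a complication | Recorded (B) | Recorded (B) |
| Non-serious, unexpected, attributed to APP, no complication diagnosed | Recorded (A) | Cannot arise |
| Non-serious, unexpected, not attributed to APP, no complication diagnosed | Only if APP is stopped (C) | Not recorded |
| Non-serious, foreseen, APP stopped, no complication diagnosed | Recorded (C) | No counterpart |
| Non-serious, foreseen, APP continued, no complication diagnosed | Not recorded | Not recorded |

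The first two rows are symmetric and sound. In the next three, an event can be recorded in the APP arm but never in the control arm. In the last, it is recorded in neither. None of the last four rows yields a valid contrast.

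**Which harms fall there**

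- *Tolerable pain.* It is foreseen, since its severe form is a named reason to stop. Short of that it does not end the session, and it is not naturally a specialist diagnosis: last row. Discomfort is also likely: the Discussion reports that most patients could hold the position for no longer than 30 min at a time, and Intervention sets a session at half an hour or more.
- *Minor skin pressure injury.* It is foreseen through the remark on pressure ulcers. A diagnosed ulcer may enter by route B; a lesser mark may not.
- *Transient chest tightness.* If APP is stopped, route C records it. The same symptom in a control patient is recorded only if the work-up that it triggers ends in a diagnosis.

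**The case against.** The strongest reply is that the plan captures far more than the adverse-event rule alone suggests. All serious events are recorded in both arms. Other complications are an outcome in both arms, and the Data collection and analysis plan compares postoperative outcomes between groups. The Discussion itself calls pressure ulcers, dislocation and fixation failure complications. Chest distress and dyspnoea prompt diagnostic tests without regard to arm. The harms listed under Intervention are described as severe and are recorded when they end APP. All of this stands, and it rules out three stronger readings that a reader might infer:

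- *That the foreseeable harms of proning go unrecorded in both arms.* They do not: serious ones, diagnosed ones and, in the APP arm, those that end treatment are all recorded.
- *That skin injury lies outside the complications outcome.* The article does not list which complications count, so neither inclusion nor exclusion can be asserted.
- *That unblinded staff judge relatedness.* The article does not say who decides this. Attributing an event to APP requires knowing that the patient had APP, and the Blinding section says that care providers are not blinded, but this remains an inference.

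A further reply is that a condensed article leaves complication lists and form fields to the full protocol. That is fair, and their absence is not the point. The point is a rule that the article states in full, and that rule governs database entry as well as reporting. Nor does severe mean serious: unbearable pain can be the first without being the second.

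**Conclusion.** The concern holds in a limited form. Non-serious adverse events cannot be recorded as such in controls. Foreseeable non-serious harms are missed in both arms unless diagnosed as a complication or, in the APP arm, followed by stopping. For that class of event the trial cannot compare its arms.

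The class is narrow clinically, but it probably contains the commonest costs of the intervention to patients. Its size in events cannot be given, because the article states no rates for these harms. The primary outcome, serious events and diagnosed complications are unaffected.

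The conclusion rests on three assumptions: the two conditions apply jointly, as written; harms that the article itself names count as expected; and control patients do not take up proning in numbers that matter. The rule should be changed, but it does not threaten the main efficacy analysis.

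**What to change.** Separate recording from reporting.

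1. **Recording.** Enter non-serious adverse events for both arms whatever their expectedness or presumed cause. The minimum is a short fixed checklist drawn from the article's own list: pain, skin pressure injury, suspected dislocation, fixation failure, chest tightness, breathing difficulty.
2. **Same window and effort.** Ask at the same times in both arms, from surgery to POD 4 and at the follow-up contacts. Each day's first APP session is supervised, so spontaneous notes alone would watch the APP arm more closely.
3. **Analysis.** Tabulate by randomised arm, with the number of patients assessed in each.
4. **Reporting.** Keep the unexpected-and-related filter for the ethics committee only.

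The cost is a few more case-report-form fields and their entry for all patients. Items should be worded neutrally, without mention of the prone position, so that the questions do not unmask blinded outcome assessors. Two limits remain: patients know their allocation, so self-reported pain stays open to reporting bias; and recruitment began in September 2021, so a change introduced in both arms on one date gives a randomised comparison only for patients randomised after it. If recruitment has ended, the trial report should state that minor harms were not collected comparably.
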